## Background

Nearly, 15.5% of all births, or more than 20 million infants worldwide, are born with low birth weight (LBW) as a result of preterm birth or intrauterine growth restriction or both [1, 2]. Preterm birth or LBW is the single largest cause of death in newborns, but the mortality can be reduced by effective newborn care interventions. However, for years, it was demonstrated that although mortality was being improved by interventions for LBW newborns, the impact on morbidity, including neurocognitive impairment and motor disabilities, was unchanged [3]. More recently, there is evidence suggesting that infant survival with improved neurodevelopmental outcomes is increasing slightly and is associated with both improved medical interventions and maternal factors [4]. However, there is also a concern of an increased risk of neurodevelopmental impairment, and this enigma needs to be addressed by a systematic study. Therefore, while evaluating the impact of any intervention on mortality in this population, it is equally important to study the risk of neurodevelopment impairments, including cerebral palsy, hearing and vision impairment, cognitive impairment, and epilepsy.

The World Health Organization (WHO) defines Kangaroo Mother Care (KMC) as a technique used in preterm and LBW infants of continuous skin-to-skin contact between mother and baby until the infant shows signs of intolerance. Exclusive breastfeeding is also encouraged as an essential component of KMC. Notably, however, it is currently recommended that continuous KMC should be initiated only once the baby is stable, meaning that the baby must be breathing spontaneously without additional oxygen [5].

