“WHO recommendations on interventions to improve preterm birth outcomes” recommends KMC for the routine care of newborns weighing 2.0 kg or less at birth, which should be initiated in health care facilities as soon as the newborns are clinically stable [6]. These babies should be provided as close to continuous KMC as possible. Intermittent KMC, rather than conventional care, is recommended for newborns weighing 2.0 kg or less at birth, if continuous KMC is not possible [6]. There is no current recommendation for KMC for unstable < 2.0 kg neonates. A recently updated Cochrane review reported 40% lower mortality in infants with birth weight < 2.0 kg given KMC compared to mortality in those who were given standard care in hospitals, at 40 to 41 weeks postmenstrual age [7]. In almost all studies included in the Cochrane review, KMC was initiated after the baby was clinically stable, with the median age at initiation of KMC 3.2 to 24.5 days [7]. Two randomized controlled trials (RCTs) comparing immediate versus conventional KMC from South Africa and Vietnam [8–10] showed favorable results for immediate KMC initiation. This data led the World Health Organization to coordinate a multi-country randomized controlled trial to evaluate the effect of initiating continuous KMC immediately after birth on survival (compared with initiation of continuous KMC a few days after birth when the baby is considered clinically stable). This RCT assessed newborn survival outcomes over the acute hospital period up to a 28-day follow-up [11]. The study enrolled 3211 infant-mother dyads with 1609 dyads in the intervention arm and 1602 in the control arm. The median daily duration (hours) of skin-to-skin contact was 16.9 h (IQR 13.0–19.7) in the intervention and 1.5 h (IQR 0.3–3.3) in the control arm. Neonatal death occurred in 12.0% and 15.7% infants, respectively, in the two arms (RR 0.75; 95% CI 0.64–0.89; *p* = 0.001). The study concluded that in infants with birth weight between 1.0 and < 1.8 kg, immediate KMC (versus conventional KMC care) resulted in a significant reduction in neonatal mortality [12]. However, in order to evaluate the overall impact of KMC, the long-term effect on neurodevelopment in the survivors should be assessed.

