### The intervention

The proposed study is a follow-up of the already concluded randomized controlled trial for evaluating the effect of immediate KMC on infant survival. The intervention and control groups were assigned during the main iKMC trial where KMC is defined as continuous skin-to-skin contact with mother or her surrogate aiming for at least 20 h per day, support for exclusive breastfeeding, and required medical care without separation from the mother as much as possible.

In the intervention group, the mother and baby remained in skin-to-skin contact from the time of randomization whereas the newborns randomized to the control group received conventional care, and the mother and baby were separated until the baby was clinically stable. The details of intervention and control arms and care of the newborns in both the groups are described in the already published protocol paper [11].

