### General principles for analysis

The analysis will be by intention to treat. The primary outcome is a composite outcome comprising cerebral palsy, hearing impairment, vision impairment, cognitive, language, socio-emotional, adaptive and motor impairment, and epilepsy, and the presence of any one or more will be considered as neurodevelopmental impairment. However, during analyses, we will also consider each of these outcomes individually. Table 1 includes the scale/tool used for outcome measurement and wherever appropriate, the cutoffs of the scales, to indicate the presence or absence of the neurological impairment.

The primary and secondary outcomes will be compared between the intervention and control groups. All planned analysis will use a 5% significance level. Risk ratios and their confidence intervals will be calculated and will be the primary analysis if the loss to follow-up is 2.5% or lower. In case the loss to follow-up for the primary outcome is greater than 2.5%, we will additionally calculate hazard ratios and their confidence intervals. Additionally, we will adjust the results for confounding using multiple logistic regression and Cox proportional hazards models if there are any important differences in baseline characteristics between immediate KMC and control groups.

If more than 5% of data is missing from interim assessments, multiple imputation will be performed, accounting for clustering by country with the number of imputations based on the percentage of missing data. Subgroup analysis will be conducted by (i) birth weight categories (1 to < 1.2 kg, 1.2 to < 1.5 kg, and 1.5 to < 1.8 kg), (ii) gestation (< 34, 34–36, >=37 weeks), and (iii) singleton/multiple birth. Secondary analysis will be limited to an analysis by compliance. This secondary analysis will present the efficacy of the intervention by average duration of skin-to-skin contact over the first 3 days of life, categorized as > =20 h/day, 10–19 h/day, and < 10 h/day.

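### The compliance analysis labels as efficacy a comparison by contact hours achieved after randomisation, with no stated adjustment between duration bands

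*Protocol article*

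**What the plan says.** General principles for analysis makes the main comparison intention to treat. It then states: "Secondary analysis will be limited to an analysis by compliance". The exposure, time window and interpretive label follow: "This secondary analysis will present the efficacy of the intervention by average duration of skin-to-skin contact over the first 3 days of life", with hours "categorized as > =20 h/day, 10–19 h/day, and < 10 h/day".

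The section does not say whether the bands apply to one arm or both, or what the comparator is. Its one statement on adjustment is conditional: models are adjusted if baseline characteristics differ importantly between the immediate KMC and control groups.

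The Background gives median daily hours of contact in the parent trial as "16.9 h (IQR 13.0–19.7) in the intervention and 1.5 h (IQR 0.3–3.3) in the control arm".

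Two places describe what governs contact. In the control arm, "the mother and baby were separated until the baby was clinically stable" (The intervention). In general, the WHO definition of KMC in the Background is "continuous skin-to-skin contact between mother and baby until the infant shows signs of intolerance".

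**The concern.** Average hours over the first 3 days are an outcome of early care, not a baseline characteristic. If sicker infants get fewer hours and sicker infants also have more impairment, the low-hours band carries a worse prognosis whatever the intervention does. Risk could then fall with rising hours even if contact had no effect. Calling that pattern efficacy invites a causal dose-response reading. The Background says that the longer-term results are meant to support policy change, so the label matters even on a secondary result.

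**Working it through.** **1. Is duration tied to prognosis within the document?**

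- Illness to hours: control infants are kept apart from the mother until stable, and KMC is defined as continuing until signs of intolerance. Both make hours depend partly on the infant's condition.
- Illness to impairment: the Discussion paragraph of the Abstract names respiratory disease, hypothermia, hypoglycaemia and infection as complications that can impair neurocognitive development.
- Adjustment: the stated trigger is imbalance between randomised arms. Arms can be well balanced while bands are not, so the trigger does not address the problem.

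The comparator is not stated, but no plausible reading keeps the randomised contrast:

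- bands within the intervention arm are an observational comparison;
- each band against all controls sets a selected subset against an unselected arm;
- arms within a band condition on a post-randomisation variable;
- arms pooled across bands mix allocation with selection.

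**2. How many controls could fall in the upper bands?**

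The inputs are the Background quartiles: control 0.3, 1.5, 3.3 h; intervention 13.0, 16.9, 19.7 h. Assumptions: they hold for the first 3 days and for survivors, and the distributions have the shapes below.

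Control arm, least-squares fit to the three quartiles:

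| Shape | Fitted quartiles (h) | P(≥10 h) | P(≥20 h) |
|---|---|---|---|
| Gamma | 0.43, 1.39, 3.33 | 3.0% | 0.2% |
| Weibull | 0.46, 1.38, 3.33 | 3.7% | 0.3% |
| Lognormal | 0.52, 1.32, 3.34 | 7.0% | 2.4% |

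A lognormal through the median and upper quartile only has σ = ln(3.3/1.5)/0.6745 = 1.169. It gives P(≥10) = 1 − Φ(ln(10/1.5)/1.169) = 5.2% and P(≥20) = 1.3%, inside the same range. No shape matches the reported lower quartile of 0.3 h well, and the tail shares are extrapolations.

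To turn shares into counts, take the planned 1100 per group. That figure reproduces. For 20% against 25%, two-sided 5%, 80% power:

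n = [1.960·√(2 × 0.225 × 0.775) + 0.842·√(0.20 × 0.80 + 0.25 × 0.75)]² / 0.05² ≈ 1094.

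- Controls at ≥10 h: 1100 × 0.030 = 33 to 1100 × 0.070 = 77.
- Controls at ≥20 h: 1100 × 0.0015 ≈ 2 to 1100 × 0.0238 ≈ 26.

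**3. What of averages between 19 and 20 h?**

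Intervention arm, normal shape: SD = (19.7 − 13.0)/(2 × 0.6745) = 4.97. Then P(19–20) = 7.0%. Truncating to 0–24 h gives 7.6%; a beta shape on 0–24 h gives 8.2%. Read literally, about 77 to 91 of 1100 intervention infants would have no band. Read as 10 to <20, none are lost.

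**The case against.** The analysis is declared secondary and by compliance, and intention to treat stays the main analysis. An article may leave comparator, arm and covariates to the full plan. Confounding is inferred from care rules, not documented: intervention infants were in contact from randomisation, and a surrogate could replace the mother, so maternal illness need not reduce hours. The Background hours are not tied to the first 3 days, and they describe all infants in the parent trial, whereas this cohort is limited to neonatal survivors.

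Much of this stands, and it limits the claim in four ways.

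- A reader might infer that a false dose-response is bound to appear, or might attach a risk ratio to it. The documents give no risk by severity or by band, so neither follows.
- A reader might infer that no effect can be estimated in the upper bands. Within-band contrasts are not stated as the plan, and 33–77 controls at ≥10 h is sparse rather than none.
- A reader might treat the 19–20 h interval as a real hole. The same section writes gestation as 34–36 followed by ≥37 weeks, which is a completed-unit convention; read that way the gap closes. It is a point of notation.
- A reader might conclude that an instrumental-variable analysis should replace the bands. The intervention also includes breastfeeding support and care without separation, so allocation can act other than through hours. The cohort is also conditioned on survival that differed by arm (neonatal death 12.0% against 15.7%).

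What does not fall away is that the article itself fixes the exposure, the window, the cut-points and the word efficacy, and the one adjustment it states is aimed at a different comparison.

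**Conclusion.** The point holds as a cheap improvement to a secondary analysis. As written, the plan presents under the name of efficacy a comparison by a post-randomisation measure that its own care rules link to infant condition, without stated adjustment between bands. A gradient could reflect prognosis; its size cannot be computed from the document. The sparsity of controls (about 3–7% at ≥10 h/day, about 2% or fewer at ≥20 h/day) depends on the fitted shapes and on the Background hours applying to the first 3 days and to survivors. It matters only if arms are contrasted within bands. The intention-to-treat comparison is not affected.

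**What to change.** Keep the duration analysis as secondary, with three changes:

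1. Describe it as an observational analysis of outcome by contact achieved, and drop the word efficacy.
2. Adjust band comparisons for baseline prognostic factors already collected: birth weight, gestation, singleton or multiple birth, site, and any recorded baseline measure of illness. State the comparator. Illness arising during the 3 days remains uncontrolled, which is a further reason for the label.
3. Write the bands as <10, 10 to <20 and ≥20 h/day.

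An instrumental-variable analysis with allocation as the instrument may be added as an optional sensitivity analysis, with its exclusion-restriction and survivor-selection limits stated.

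The cost is a little more modelling and a weaker label. The changes are to wording and covariates.

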### Study oversight

The study Steering Committee comprises all PIs from study sites, Bill and Melinda Gates Foundation representatives, and WHO technical staff functioning as its secretariat. This committee is responsible for designing and implementing the study in a harmonized way. Study PIs are responsible for contributing to the development of the research proposal, study manual, data management system, outcome measurement and data collection, data analysis and interpretation, and dissemination of results. All activities are facilitated and supported by WHO headquarters. On a fortnightly basis, the sites submit a brief status report to WHO. A formal progress report is submitted by each site every year.

The study is coordinated by a technical team from WHO headquarters, ensuring arrangements are in place to support teams in any challenges being faced to implement this study. WHO technical staff conducted intensive training at the beginning of the study. The technical team performs monitoring visits to each site every year. Monitoring visits have the dual function of identifying problems and supporting the sites in improving data collection, follow-up, and monitoring.

A Technical Advisory Group (TAG) has been set up in the field. The TAG members serve in their individual capacity and reviewed the final research protocol for any major concern prior to trial implementation. TAG members’ terms of reference also include revision of manual of operations, study forms, and consent forms and advise on practical issues in implementing the trial in the field.

There is no data and safety monitoring board constituted for this study as this is a prospective follow-up study of a cohort of trial participants.

## Discussion

This international multi-site study is the first of its kind aiming to assess the effect of immediate KMC on long-term outcomes. The literature has demonstrated an immediate benefit of KMC in stable neonates and is part of WHO guidelines for newborn care [5, 6]. More recently, the main iKMC trial showed that the benefits of KMC can be extended to unstable low birth weight babies, beginning right at birth, and iKMC had a 25% lower risk of death at 28 days than those who received conventional care with Kangaroo Mother Care initiated after stabilization [12]. With the parent trial successfully conducted across these sites, there is no better opportunity to study the effect of this intervention on long-term outcomes. The follow-up study has the objective of elaborate and precise assessment of all the domains of neurodevelopment, including cerebral palsy (HINE), developmental delay (BSID III), hearing, vision, and epilepsy screening which would be evaluated by trained personnel ensuring optimal standardization on the large sample size in the five LMIC countries. The training and standardization conducted as part of this study have already strengthened the infrastructure and supported capacity building in the participating sites. This can be scaled up in the future at various tertiary centers in LMICs, in order to ensure quality, follow-up care for each and every mother-NICU/NICU graduate.

In addition, the final results will provide crucial insights and a higher level of evidence for the much-awaited long-term outcome of immediate KMC in the vulnerable sick low-birth-weight neonates. If proven effective, this intervention would be a value addition to the set of cost-effective strategies in reducing neurological impairment in resource-limited countries.

### Study status

The trial is ongoing in all five sites—Ghana, India, Malawi, Nigeria, and Tanzania. The first participant was recruited on 11 January 2019. Participant recruitment and completion of all assessments are expected to be completed by 20 July 2022. The current protocol is version 3.2 dated 7 April 2021.

## Data Availability

The datasets generated during the current study will be available from the corresponding author on reasonable request.

## Abbreviations

KMC: Kangaroo Mother Care
iKMC: Immediate Kangaroo Mother Care
LIMC: Low- and middle-income income countries
LBW: Low birth weight
WHO: World Health Organization
RCT: Randomized controlled trial
HINE: Hammersmith Infant Neurological Examination
BSID III: Bayley Scales of Infant and Toddler Development
ILAE: International League against Epilepsy
ABR: Auditory brainstem responses
IRB: Institutional Review Board
GCP: Good Clinical Practice
PI: Principal investigator
PHQ-9: Patient Health Questionnaire-9
TOT: Training of trainers
TAG: Technical Advisory Group
